**Figure 1 FIG1:**
[figure not shown]
Flowchart of the study

Study participants

Eligibility Criteria

Initially, a baseline study was conducted to assess the caregiving burden among female informal caregivers of cancer patients. Subsequently, in this study, individual caregivers are enrolled based on their experiences with mild-to-moderate, moderate-to-severe, and severe burdens, as determined using the Bangla version of the Zarit Burden Interview (ZBI)-22 [22]. The inclusion criteria were as follows: females aged 18 years or older and those who have been providing care to a cancer-diagnosed patient for at least six months. The exclusion criteria included those who refused to collaborate with the ongoing study, caregivers receiving financial compensation or employed as formal caregivers, those experiencing extremely traumatic events that occurred during the study (such as the deaths of loved ones or patients, separations, etc.), caregivers undergoing psychotropic drug treatment, and those without smart mobile devices at home.

Sample Size

We used the G*Power software (Version 3.1.9.7) to calculate the sample size. An effect size of 0.72 was estimated based on a similar previous study that examined the caregiving burden among family caregivers [23]. The sample size required for the study was 84 caregivers, based on a power analysis of the difference between two independent means (two groups), a confidence level of 0.95, and a statistical power of 0.90. Eighteen additional caregivers will be recruited to compensate for potential dropouts. Following a 20% dropout rate, the total number of participants was 102, 51 in the intervention group (IG) and 51 in the control group (CG).

Data Collection and Follow-Up

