Data will be collected at baseline (before the intervention), midline (after three months of intervention), and endline (after six months of intervention), through face-to-face interviews with participants. Sociodemographic data will be collected from two categories: caregivers and patients. Patients' basic characteristics such as sex, age, education, and marital status will be obtained directly from the patients. Additionally, relevant cancer-related information including cancer stage, type of cancer, duration of cancer, medical or other types of insurance coverage, and treatment type will be collected from hospital records. Data on caregivers' sociodemographic characteristics includes age, marital status, education level, employment status, monthly family income, presence of chronic diseases, relationship with the patient, duration of caregiving (months), and daily caregiving time (hours). Moreover, the ZBI-22 [22], Hospital Anxiety Depression Scale (HADS) [24], and World Health Organization Quality of Life Instrument (WHOQOL-BREF) [25] will be used to assess the level of burden, anxiety, depression, and QOL, respectively, all of which were validated and adopted in the local language, Bengali.

Randomization

After computer-generated stratification, participants will be randomly assigned according to their degree of burden, anxiety, and depression. In this study, there will be a 1:1 open-label randomization for either the IG or the CG. Randomization will be performed by a trained research assistant not involved in the intervention. The researchers will start organizing the study as soon as the research assistant informs them which participants are assigned to the IG or CG.

Intervention

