Schedule	Intervention group	Control group
First month	First week: We will provide videos on information on cancer, symptom management, and the BRT with individual face-to-face training on the BRT by a trained nurse who will receive training from a physiotherapist. Second, third, and fourth weeks: Phone call and SMS reminder (once a week) for follow-up and a question-and-answer session.	Usual care
Second month	First week: We will provide a video on maintaining and enhancing relationships. Second, third, and fourth weeks: Phone call and SMS reminder (once a week) for follow-up and a question-and-answer session.	Usual care
Third month	First week: We will provide a video on problem-solving. Second, third, and fourth weeks: Phone call and SMS reminder (once a week) for follow-up and a question-and-answer session.	Usual care
Fourth month	First week: We will provide videos on stress and coping. Second, third, and fourth weeks: Phone call and SMS reminder (once a week) for follow-up and a question-and-answer session.	Usual care
Fifth month	First week: We will provide a video on self-care. Second, third, and fourth weeks: Phone call and SMS reminder (once a week) for follow-up and a question-and-answer session.	Usual care
Sixth month	First week: We will provide a video on effective communication. Second, third, and fourth weeks: Phone call and SMS reminder (once a week) for follow-up and a question-and-answer session.	Usual care

Endpoints

The primary outcome involves assessing the change scores obtained from the ZBI. Meanwhile, the secondary outcomes are as follows: (1) assessment of changes in anxiety and depression levels by the HADS and (2) changes in QOL, as measured by the WHOQOL questionnaire. Both primary and secondary outcomes will be assessed at baseline, midline, and endline in both the IG and CG.

Measurements

ZBI

As a measure of caregiver burden, we will use the ZBI, which consists of 22 items [22]. The frequency of experiencing certain caregiver-related challenges is expressed on a Likert scale ranging from 0 to 4 as follows: 0=never, 1=rarely, 2=sometimes, 3=quite frequently, and 4=nearly always. Where higher scores represent a higher burden, the scores are the following: 0-21=little or no burden, 21-40=mild-to-moderate burden, 41-60=moderate-to-severe burden, and 61-88=severe burden.

HADS

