The HADS will be used to evaluate the anxiety and depression levels [24]. Among the 14 items on a scale from 0 to 3, higher scores indicate anxiety or depression and the severity of their experience. Anxiety and depressive symptoms will be categorized according to predetermined criteria as follows: 0-7=normal levels, 8-10=borderline abnormal levels, and 11-21=abnormal levels.

WHOQOL-BREF

The WHOQOL-BREF will be used to assess the caregiver's QOL [25]. This instrument is particularly designed to evaluate multiple QOL components, including social interactions, environmental variables, psychological well-being, and physical health. A total of 26 items will rate their experiences on a Likert scale ranging from 1 to 5.

Data safety monitoring plan

Participants in this study have no minimal risk, and the researcher will treat all their personal information, including names, phone numbers, and addresses, as confidential and keep them secure. Confidentiality procedures will be implemented to ensure that participants' information is kept secure. Only members of our survey research team will have access to the data obtained from the questionnaires.

Statistical analysis

The IBM SPSS Statistics for Windows, Version 25.0 (Released 2017; IBM Corp., Armonk, New York, United States) will be used to evaluate the data. The results of the IG and CG will be compared using an intention-to-treat analysis. Continuous data will be presented as mean and standard deviation (SD), while categorical data will be represented as frequencies and percentages. Baseline data will be analyzed using various statistical tests, such as the chi-squared test, t-test, Mann-Whitney U test, Pearson's X2 test, or Fisher's exact test, to compare the two groups (IG and CG). A specific test will be employed depending on the variable type and distribution of the data. The mean values of the ZBI, HADS, and WHOQOL-BREF will be compared between the two groups at baseline, midline, and endline to assess the efficacy of the intervention. Comparisons will be performed using independent t-tests. Additionally, two-way repeated-measures analysis of variance (ANOVA) will be employed to evaluate changes in outcomes over time within each group (from baseline to endline). This analysis considers the IG, time, and their interactions. Statistical significance will be set at p<0.05. The latest observation carried forward approach will be applied to data imputation to resolve missing data.

Ethical considerations

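### The efficacy t-tests of raw visit means do not match the change-score primary outcome and ignore baseline and the stratification factors; they are valid but inefficient, and no analysis is named primary

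*Protocol article*

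**What the plan says.** All references are to the protocol article.

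- **Endpoints:** "The primary outcome involves assessing the change scores obtained from the ZBI". HADS and WHOQOL-BREF changes are secondary.
- **Randomization:** after computer-generated stratification, "participants will be randomly assigned according to their degree of burden, anxiety, and depression".
- **Statistical analysis:** "The mean values of the ZBI, HADS, and WHOQOL-BREF will be compared between the two groups at baseline, midline, and endline", for the declared purpose of judging efficacy. The next sentence names the test: "Comparisons will be performed using independent t-tests". No covariate or stratification factor is mentioned.
- **Statistical analysis, continued:** a two-way repeated-measures ANOVA is added, with group, time and their interaction. It is described as examining change over time inside each group. The Abstract also lists this ANOVA as a means of evaluating outcomes.
- **Sample Size:** 84 caregivers, "based on a power analysis of the difference between two independent means (two groups"), with "a confidence level of 0.95, and a statistical power of 0.90". The effect size: "An effect size of 0.72 was estimated based on a similar previous study". The total is 102 after allowing for dropout.

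Neither the t-tests nor the ANOVA is designated as the primary analysis.

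**The concern.** Three statements in the same document do not fit together. The endpoint is a change, the named efficacy test compares raw levels at each visit, and the allocation is balanced on baseline factors that no analysis includes. The protocol fixes the endpoint and the test itself, so this is not detail left to a later analysis plan.

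Two things are at stake. First, baseline ZBI is likely to predict month-6 ZBI, and a test that ignores it has a wider confidence interval than necessary. Second, when allocation is balanced on a prognostic factor and the analysis omits that factor, the usual standard error is too large, so the test rejects a true null hypothesis less often than 5% of the time.

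The t-test at baseline also sits in the list of efficacy comparisons, although it precedes any intervention and can say nothing about efficacy.

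**Working it through.** **Inputs from the document.** d = 0.72, power 0.90, confidence level 0.95, N = 84 (42 per arm) before dropout (Sample Size); "Statistical significance will be set at p<0.05" (Statistical analysis). The test is taken as two-sided because that reproduces N; one-sided would give 68.

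**Assumptions.** The document gives no SD and no baseline-endline correlation r. I take r from 0.3 to 0.7 and read d = 0.72 on the raw endline SD.

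**Step 1: the plan's own figure.** For an unadjusted two-sided t-test with 42 per arm, the noncentrality is d × √(n/2) = 0.72 × √21 = 3.30 on 82 df. Power is 0.903, and 42 per arm is the smallest size reaching 0.90. The stated 84 reproduces exactly.

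**Step 2: other tests at 42 per arm.**
- ANCOVA: residual variance is multiplied by 1 − r², so the noncentrality is 3.30/√(1 − r²) on 81 df.
- Change-score t-test: variance is multiplied by 2(1 − r), so the noncentrality is 3.30/√(2(1 − r)) on 82 df.

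| r | 1 − r² | Raw t-test | ANCOVA | Change-score t-test | N for 90% power, ANCOVA |
|---|---|---|---|---|---|
| 0.3 | 0.91 | 0.903 | 0.928 | 0.787 | 76 |
| 0.4 | 0.84 | 0.903 | 0.945 | 0.845 | 72 |
| 0.5 | 0.75 | 0.903 | 0.964 | 0.903 | 64 |
| 0.6 | 0.64 | 0.903 | 0.983 | 0.954 | 54 |
| 0.7 | 0.51 | 0.903 | 0.995 | 0.988 | 44 |

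The change-score t-test falls below the raw t-test when r < 0.5, because 2(1 − r) then exceeds 1.

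**Step 3: stratified allocation.** I simulated 84 participants, with allocation balanced within three roughly equal baseline burden strata.

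| r | Type I error, raw t-test | Type I error, ANCOVA |
|---|---|---|
| 0.3 | 0.044 | 0.052 |
| 0.5 | 0.029 | 0.051 |
| 0.7 | 0.014 | 0.052 |

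(8,000 runs each; Monte Carlo standard error at 0.05 is √(0.05 × 0.95/8000) = 0.002.)

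At d = 0.72 the raw t-test has power of about 0.92, 0.93 and 0.94 for r = 0.4, 0.5 and 0.6. Simulated to three decimals, the pairs (t-test against ANCOVA) are 0.919 and 0.948, 0.925 and 0.963, 0.938 and 0.983. The gains are 0.029, 0.038 and 0.045, or about 3 to 5 percentage points.

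**Step 4: the repeated-measures ANOVA.** Its group-by-time term does test a difference in change. Assume equal correlation between visits and half the effect at midline. The omnibus interaction at 42 per arm then has power of about 0.70, 0.76, 0.85 and 0.92 for r = 0.3, 0.4, 0.5 and 0.6. This is below ANCOVA throughout, and below the raw t-test up to r = 0.5.

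**The case against.** The strongest reply is the repeated-measures ANOVA. Baseline is one of its time levels, its interaction asks whether change differs between arms, and the Abstract names it for evaluating outcomes. A reader might infer from the t-tests that baseline information is discarded across the whole plan. The document does not support that. But the ANOVA is presented as an addition aimed at change inside each group, it treats baseline as an outcome rather than a covariate, and it contains no stratification factor. It softens the point without removing it.

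Three other strong readings also fail:

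- **That the t-test is biased or inflates false positives.** It is unbiased under randomisation, and after stratified allocation it errs on the conservative side.
- **That the trial is underpowered.** On its own inputs it is not: it was sized for this very test and reaches 0.903 with 84 analysed.
- **That a chance baseline imbalance is carried whole into the endline difference.** On average only a fraction r of it carries over. Balancing within burden strata also limits it: in simulation the SD of the between-arm baseline difference falls from about 0.22 to 0.10 SD units.

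It is also fair to say that the baseline t-test may be loose wording, since one sentence covers all three visits, and that it has no effect on the endline inference.

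What remains is the mismatch between endpoint, allocation and test, the avoidable loss of precision, and the absence of a named primary analysis.

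**Conclusion.** The point holds as one of alignment and efficiency, not validity. The named efficacy test does not correspond to the change-score endpoint and ignores both the baseline score and the stratification factors. The additional ANOVA uses baseline only through its interaction term.

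At the design effect, and for an assumed r of 0.4 to 0.6, adjustment raises power from 0.90 to about 0.94 to 0.98 under simple allocation. Set against the t-test under burden-stratified allocation, the gain is about 3 to 5 points. Adjustment also brings type I error back to about 0.05, from 0.044 to 0.014 over r of 0.3 to 0.7.

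Every one of these gains depends on the assumed r. The simulation also stratifies on burden alone, in assumed thirds, whereas the trial stratifies on anxiety and depression too. The mismatch and the missing primary designation depend on no assumption.

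**What to change.** Name a single primary analysis: the between-arm difference in month-6 ZBI from ANCOVA, or the month-6 contrast of a mixed model, with baseline ZBI, HADS-anxiety and HADS-depression as continuous covariates. These carry the stratification factors. With baseline ZBI in the model, the adjusted difference in month-6 score equals the adjusted difference in change, so the change-score endpoint is respected.

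Analyse HADS and WHOQOL-BREF in the same way, each with its own baseline value as a covariate. Keep the repeated-measures analysis as supportive. Stop listing the baseline t-test among the efficacy comparisons.

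Do not substitute an unadjusted change-score t-test: it matches the endpoint in name but has less power than the raw t-test if r is below 0.5 (0.787 at r = 0.3).

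The cost is analysis wording only. ZBI, HADS and WHOQOL-BREF are already collected at baseline, and the sample size need not change. Because the trial is open-label, the change should be dated and recorded before any outcome data are compared by arm.

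### ZBI change is the primary outcome, but efficacy is tested on raw means at three visits plus an ANOVA, all at p<0.05, with no test named to decide

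*Protocol article*

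**What the plan says.** Protocol article, Endpoints: "The primary outcome involves assessing the change scores obtained from the ZBI". The same section adds: "Both primary and secondary outcomes will be assessed at baseline, midline, and endline in both the IG and CG". No visit is singled out.

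Protocol article, Statistical analysis, on the group means of all three scales (burden, anxiety and depression, quality of life): these "will be compared between the two groups at baseline, midline, and endline to assess the efficacy of the intervention". The next sentence gives the test: "Comparisons will be performed using independent t-tests". Then: "Additionally, two-way repeated-measures analysis of variance (ANOVA) will be employed to evaluate changes in outcomes over time within each group". The model is described so: "This analysis considers the IG, time, and their interactions". One threshold covers everything: "Statistical significance will be set at p<0.05".

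Protocol article, Sample Size: 84 caregivers, from a comparison of two independent means with effect size 0.72, confidence 0.95 and power 0.90.

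**The concern.** The endpoint and the test do not match. The endpoint is a change score; the efficacy t-tests use the raw mean at each visit. One of those visits is baseline, which precedes the intervention and so cannot show efficacy. Baseline comparability already has its own sentence earlier in the section, so the efficacy sentence is not just a description of a baseline table.

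The ANOVA is described as looking at change inside each arm, yet the terms listed for it include the arm-by-time interaction, which is a contrast between arms. A reader cannot tell which of its terms bears on efficacy.

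Several ZBI results could therefore each be presented as the trial's answer: midline, endline, interaction or arm effect. The trial is open-label, and its Conclusions recommend national use if the findings are positive. What counts as positive should be fixed before the data are seen.

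**Working it through.** **1. The plan's own figure.** Inputs from Sample Size: d = 0.72, alpha = 0.05 (confidence 0.95), power 0.90, 1:1 allocation. For a two-sample t-test with n per arm, the noncentrality is d × √(n/2) on 2n − 2 degrees of freedom. With n = 42 it is 0.72 × √21 = 3.30 on 82 df, and two-sided power is 0.903. So 42 per arm, 84 in total, is reproduced. A one-sided test would need only 68. The trial is thus sized for one two-sided comparison of two means.

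**2. The routes to a positive ZBI result.** The text lists a midline t-test, an endline t-test, the arm-by-time interaction and the arm main effect. The baseline t-test is left out because it cannot support an efficacy claim.

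**3. Chance of at least one p<0.05 with no true effect.** Were the tests independent, the chance would be 1 − 0.95^k: 9.75% for two tests, 14.3% for three, 18.5% for four. They are correlated, so these overstate it. The rates were simulated with 42 per arm, three visits, equal correlation r between visits, simple 1:1 randomisation and 20,000 replicates. The documents do not give r; 0.3 to 0.9 is an assumption.

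| r | Endline t-test alone | Midline or endline | + interaction | + arm effect |
|---|---|---|---|---|
| 0.3 | 5.00% | 9.44% | 12.24% | 14.19% |
| 0.5 | 5.15% | 9.03% | 12.39% | 13.65% |
| 0.7 | 4.97% | 8.35% | 12.34% | 13.05% |
| 0.8 | 4.86% | 7.85% | 11.74% | 12.30% |
| 0.9 | 5.09% | 6.98% | 11.34% | 11.66% |

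Simulation standard error is √(0.05 × 0.95/20,000) = 0.15 points near 5%, and about 0.25 points near 14%. A correlation that decays with time (0.5 or 0.7 between adjacent visits) gives 8.3-8.8%, 12.3-12.6% and 13.5-13.7% for the last three columns. With 51 per arm and r of 0.3, 0.5 and 0.7, the last column is 14.2%, 13.3% and 13.2%. The interaction alone stays near 5%, so each single test is sound and the excess comes from having a choice.

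**4. A limit on these figures.** The Randomization section stratifies on burden, anxiety and depression, without giving cut-points or blocks. If stratification balances baseline ZBI, unadjusted tests become conservative. With perfect balance, the variance of the endline difference falls by the factor 1 − r². At r = 0.5 the nominal cut-off of 1.96 then acts as 1.96/√0.75 = 2.26, and the endline test rejects about 2.4% of the time, not 5%. The table is therefore the case without such balance. The more the stratification balances baseline ZBI, and the higher r is, the lower the true rates.

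**5. Does the remedy fit the endpoint?** Write ZBI at six months = a + b × arm + c × baseline ZBI. Subtracting baseline from both sides gives change = a + b × arm + (c − 1) × baseline ZBI. The treatment effect b, its standard error and its p-value are the same, so one baseline-adjusted test serves the raw score and the change score alike. Adjustment scales the residual variance by 1 − r². At r = 0.3 the effect in residual SD units is 0.72/√0.91 = 0.75, so 84 remains enough apart from the loss of one degree of freedom.

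**The case against.** The strongest reply is that this is a condensed article. Ranking of tests and rules on multiplicity are commonly left to an analysis plan, which may exist and is not shown. That stands as far as it goes: silence on ranking would not alone be a finding. What the article does state is the problem, namely a change-score endpoint, raw-mean t-tests assigned to efficacy, baseline among them, and an ANOVA described by within-arm change. An analysis plan would have to override some of this.

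The Introduction frames the question over six months, and the ANOVA sentence refers to baseline through endline. This points to six months as the natural horizon but does not exclude a claim at midline.

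Under randomisation, raw and change scores estimate the same between-arm difference in expectation. That is correct: the mismatch leaves the choice of test open; it does not change the treatment effect being estimated.

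Three stronger readings are tempting and are not supported:
- That the false-positive rate is above 5% as a matter of fact. The article states no rule that any one significant result means success.
- That the stated power of 0.90 is wrong. It was claimed for one comparison of two means and fits an endline t-test with 42 per arm; it was never claimed for the interaction.
- That efficacy will be judged from separate tests inside each arm. The wording invites this, but no per-arm test is named and the listed model includes a between-arm term.

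**Conclusion.** The point holds as an inconsistency in what the article fixes: the efficacy tests do not match the primary outcome, and no test, visit or ANOVA term decides. Its size is conditional. If any significant ZBI result may be read as success, the false-positive rate is about 7-10% on the two post-baseline t-tests and about 12-14% with the interaction and arm effect added, against 5% for a single named test. This rests on visit correlations of 0.3-0.9 and on randomisation that does not balance baseline ZBI; close balance would reduce it. Only the ZBI is counted, since the HADS and WHOQOL-BREF are secondary. The need to name one test does not depend on the exact rate.

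**What to change.** In Statistical analysis:
- Name one deciding test: the between-arm difference in ZBI at six months, adjusted for baseline ZBI (ANCOVA), two-sided 5%. State that it gives the same treatment effect for change from baseline, which reconciles it with Endpoints.
- Label the midline comparison, the ANOVA terms and any within-arm change as supportive, with no efficacy claim drawn from them.
- Remove baseline from the visits at which efficacy is compared.
- Describe the ANOVA by its between-arm group-by-time interaction.

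The cost is a few sentences. The required 84 and the recruitment target of 102 are unchanged by this. The sponsor gives up the chance to claim success on midline, or on any other ZBI test, alone.
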